## Abstract

**Background:**

Secondary treatment of arteriosclerosis may be applicable for the primary prevention of atherosclerosis in diabetic patients. This prospective, 2-year follow-up study was designed to determine the efficacy and safety of antiplatelet therapy in the prevention of atherosclerosis of diabetic subjects.

**Methods:**

Patients with type 2 diabetes and arteriosclerosis obliterans from the Eastern Asian countries were registered online and randomly assigned either to the aspirin group (81–100 mg/day) or the cilostazol group (100–200 mg/day) in this international, 2-year, prospective follow-up interventional study.

**Results:**

The primary study endpoint was changes in right and left maximum intima-media thickness of the common carotid artery. Secondary endpoints include changes in right and left maximum intima-media thickness of the internal carotid artery; semiquantitative evaluation of cerebral infarction by magnetic resonance imaging; cardiovascular events including sudden death, stroke, transient cerebral ischemic attacks, acute myocardial infarction, angina, and progression of arteriosclerosis obliterans; overall death; withdrawal; and change in ankle-brachial pressure index.

**Conclusion:**

This is the first study to use an online system that was developed in Asian countries for pooling data from an international clinical trial. These findings are expected to help in the prevention of diabetic atherosclerosis and subsequent cardiovascular and cerebrovascular disease.

## Background

Westernization of lifestyle has led to an explosive increase in the number of diabetic patients and an increase in diabetic atherosclerosis in Eastern Asian countries [1,2]. This is of great concern for the future of patients and health systems in East Asia, and is a problem that requires immediate and careful evaluation. With this in mind a cooperative, multinational research group in Japan, Korea, China, and Phillippine has been formed to investigate the potential for antiplatelet medication to prevent the occurrence and progression of diabetic atherosclerosis in Asian patients.

The rationale for the study is based upon the finding that the primary incidence rate of coronary artery disease (CAD) in diabetic patients is similar to the secondary incidence rate of CAD in nondiabetic patients. This finding suggests that secondary treatment of atherosclerosis is applicable to the primary prevention of arteriosclerosis in diabetic patients. Antiplatelet drugs are widely reported to be effective in preventing the recurrence of atherosclerosis. In one study [3], type 2 diabetic patients with early-stage carotid atherosclerosis who were given aspirin showed a slight progression of intima-media thickness (IMT) of the carotid artery (0.033 ± 0.010 mm/year). In another study [4], similar patients given cilostazol showed negligible change in IMT (0.00 ± 0.16 mm/3 years). However, the primary preventive and secondary therapeutic effects of these two drugs have not been sufficiently investigated in the Asian diabetic patient population. We therefore initiated an international, 2-year prospective follow-up interventional study to clarify the efficacy and usefulness of aspirin and cilostazol in the primary prevention and secondary treatment of diabetic atherosclerosis in Asian patients. Assessment will be performed by chronologically observing the intima-media thickness (IMT) of the carotid artery, which is used as a surrogate endpoint of atherosclerosis, and by analyzing the occurrence and progression of large-vessel complications in patients with type 2 diabetes and mild atherosclerosis [5,6].

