***Inclusion criteria:***
1) Type 2 diabetes mellitus
2) Age between 40 to 85 years
3) Clinical findings suggestive of arteriosclerosis obliterans (ASO)
Note 1: Definition of ASO: Patient who has the following lesions in either of the lower limbs
• ABI (ankle brachial pressure index) < 1.0
• A weakened or bilaterally different pulsation of popliteal artery or dorsal artery of foot
• clinical signs and symptoms suggestive of ASO

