**Secondary endpoints:**	
IMT*: Variation of right and left max IMT-ICA	

*Variation is measured by the IMT Evaluation Committee by using a diagnostic software application called IntimaScope^® ^while the allocations are blinded.

The following exclusion criteria were set: those with type 1 or secondary diabetes, severe ASO (greater than a Fontaine IIb category) or grade 4 or higher cerebral infarction on the Modified Rankin Scale, and medical history of angina or myocardial infarction. In addition, patients with a range of concomitant comorbidities including severe hepatic or renal dysfunction, congestive heart failure, bleeding disorders, or familial hypercholesterolemia, those with allergy or hypersensitivity to the investigational drugs, pregnant or lactating women, or women wishing to become pregnant, were excluded. Written informed consent has been obtained from all patients, and the study has been reviewed by the ethics review board of the all institutes participated in this study if the institute had the ethics review board.

Registration of patients was preformed at the administration office of the Diabetic Atherosclerosis Prevention by Cilostazol (DAPC) Study via the Internet, and once enrolled, subjects were randomly assigned to the aspirin group (81–100 mg/day; group A) or the cilostazol group (100–200 mg/day; group C). Patients who were already receiving antiplatelet drugs were assigned without a washout period. The study period will be 2 years after the registration of subjects (registration period: November 2004 to March 2006; full study duration: December 2004 to March 2008).

The primary study endpoint is the change in right and left maximum IMT of the common carotid artery (CCA) and mean IMT-CCA change. Secondary endpoints are the change in right and left maximum IMT of the internal carotid artery; semiquantitative evaluation of cerebral infarction by MRI measurement; cardiovascular events including sudden death, occurrence or recurrence of stroke, transient cerebral ischemic attacks, acute myocardial infarction, angina, and progression of ASO; overall death; withdrawal; and change in ABI.

Investigations will be performed at the start of the study, after 1 year, at the conclusion of the study, and at the time of any discontinuations or changes in dosage. Any adverse reactions will also be assessed.

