## Discussion

The aim of this study is to clarify the efficacy and usefulness of two different antiplatelet drugs, aspirin and cilostazol, in the prevention of occurrence or progression of atherosclerosis in patients with type 2 diabetes. Antiplatelet drugs such as aspirin have been shown to be effective in preventing the recurrence of atherosclerosis in these patients. However, effectiveness of aspirin on diabetic patients is still controversial. Kodama and colleagues [3] have reported that both aspirin and ticlopidine significantly reduced, but did not halt, progression of increase in IMT in patients with type 2 diabetes and early-stage carotid atherosclerosis. Recently, the Primary Prevention Project (PPP) Trial showed that a significant reduction of the total cardiovascular events was observed in nondiabetic subjects but no significant reduction was observed in diabetic subjects [7]. In contrast, Shinoda-Tagawa and colleagues [4] showed that similar patients given cilostazol showed a negligible change in IMT over a 3-year follow-up period. Cilostazol is also shown to be effective in reducing occurrence of cerebral infarction in diabetic subjects [4]. We feel that the therapeutic effects resulting from the differing mechanisms of action of aspirin and cilostazol have not been sufficiently investigated in this patient population.

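### The aims claim efficacy of antiplatelet therapy and primary prevention of atherosclerosis, but the design supports only a comparison of cilostazol with aspirin in patients with findings of ASO

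*Protocol article*

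**What the plan says.** The aim is stated three times, each time more broadly than a comparison of two drugs.

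- Abstract, Background: to "determine the efficacy and safety of antiplatelet therapy in the prevention of atherosclerosis of diabetic subjects". This is a claim about a class.
- Background: "to clarify the efficacy and usefulness of aspirin and cilostazol in the primary prevention and secondary treatment of diabetic atherosclerosis". This is a claim about each drug, in two settings.
- Discussion: the efficacy and usefulness of the two drugs "in the prevention of occurrence or progression of atherosclerosis in patients with type 2 diabetes".

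The design is narrower. Under Study design and protocol, "subjects were randomly assigned to the aspirin group (81–100 mg/day; group A) or the cilostazol group (100–200 mg/day; group C"). The entry criteria in Table 1 require "Clinical findings suggestive of arteriosclerosis obliterans (ASO"), the Abstract describes the enrolled patients as "Patients with type 2 diabetes and arteriosclerosis obliterans from the Eastern Asian countries", and the Background calls them patients with mild atherosclerosis. Patients already taking antiplatelet drugs are randomised without washout. The statistical paragraph sizes the trial for a significant difference between the two groups and plans between-group methods. On the comparator, the Discussion says: "However, effectiveness of aspirin on diabetic patients is still controversial".

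**The concern.** A statement of aim fixes what a trial may later conclude. Efficacy of a drug or a class means an effect against not giving it, and this trial has no such contrast. An active control can stand in for the missing arm if its own effect is accepted, but the article says that aspirin's effect in this population is not settled.

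Two readings of the results are therefore at risk. If carotid IMT is stable in both arms, the stated aim would be answered by saying that antiplatelet therapy works, although untreated patients might have been stable too. If the arms do not differ, the aim would be answered by saying that both drugs are effective, although it could equally be that neither is. In addition, any finding would come from patients selected for signs of arterial disease, and would not bear on preventing that disease from arising.

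**Working it through.** **What the contrast identifies.** Let μA and μC be the mean 2-year IMT changes on aspirin and cilostazol, and μ0 the mean change without antiplatelet treatment, all in this population.

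- The trial estimates μC − μA.
- Efficacy of cilostazol is μC − μ0, and efficacy of aspirin is μA − μ0.
- μC − μA = (μC − μ0) − (μA − μ0), so μ0 cancels. Any value of μ0 fits any trial result. In particular, μC = μA holds both when the two drugs work equally well and when neither works.

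**Can the cited figures supply μ0?** The Background gives 0.033 mm/year on aspirin and 0.00 mm over 3 years on cilostazol. Scaled linearly to 2 years (an assumption), these are 2 × 0.033 = 0.066 mm and 0.00 mm. Both are on treatment and come from separate studies. The article gives no rate for untreated patients.

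**Can change within an arm supply it?** No. There is no concurrent untreated group, and for patients already on antiplatelet drugs the baseline scan is itself on treatment.

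**The plan's own figure.** The article gives 408 patients without stating the difference, SD or power behind it, so the figure can be neither confirmed nor refuted. Assuming 1:1 allocation (204 per arm), two-sided 0.05 and a 2-year difference of 0.066 mm, the common SD that would give 408 is:

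- 80% power: 0.066 / [(1.960 + 0.842) × √(2/204)] = 0.238 mm
- 90% power: 0.066 / [(1.960 + 1.282) × √(2/204)] = 0.206 mm

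With a 1-year difference of 0.033 mm the SDs halve, to 0.119 and 0.103 mm. Whatever the true inputs were, the article says that 408 serves a difference between its two groups. That is the aspirin–cilostazol contrast, not drug against no drug.

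**Aims against design.**

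| Stated aim | Needed to answer it | In the design |
|---|---|---|
| Efficacy of antiplatelet therapy | Antiplatelet arm against untreated arm | Both arms antiplatelet |
| Efficacy of each drug | Each drug against no drug, or a comparator of accepted effect | Comparator's effect called controversial |
| Primary prevention, or occurrence, of atherosclerosis | Patients without atherosclerotic findings | Findings suggestive of ASO required |
| Secondary treatment, or progression | Patients with disease | Present, but the effect is relative only |

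**The case against.** **The design is openly comparative.** The statistical paragraph is between-group throughout, the Discussion speaks of two drugs with different mechanisms, and no passage plans an equivalence claim or a within-arm test. This stands: the analysis is consistent with a comparison, and the fault lies in the aims. A reader might infer that the plan lacks an equivalence or non-inferiority margin. It needs none, because it is sized to find a difference.

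**Aspirin has outside support.** The Discussion cites a study in which aspirin and ticlopidine reduced IMT progression in type 2 diabetic patients. A clear advantage of cilostazol would then support its efficacy indirectly: if aspirin does no harm (μA ≤ μ0), μC < μA implies μC < μ0. This stands as an argument that depends on that assumption. It does not help after a null result, and the article itself leaves aspirin's effect open.

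**Part of the trial is primary prevention.** Table 1 excludes prior angina and myocardial infarction, so an infarction or angina recorded as an endpoint would be a first one. Lower-grade cerebrovascular disease is allowed but not required, and entry needs findings only suggestive of ASO. So it goes too far to say that no patient is in primary prevention of anything. First coronary events can be described, though only as cilostazol against aspirin. The aims, however, speak of preventing atherosclerosis.

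**The trial may seem too imprecise to support a null result.** With 200 per arm and an assumed SD of 0.16 mm, the 95% half-width is 1.96 × 0.16 × √(2/200) = 0.031 mm, which a reader might set beside the 0.033 mm/year on aspirin. The documents do not support that comparison. The follow-up is 2 years, so the matching figure is 0.066 mm, and the SD is borrowed from an unlabelled ± value over 3 years. SDs of 0.10 to 0.24 mm give half-widths of 0.020 to 0.047 mm, so an estimate near zero would exclude 0.066 mm throughout that range. The point here is what the contrast identifies, not its precision.

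**The analysis plan is not shown.** It may well say how a null result is to be worded. It cannot add an untreated arm or a population free of atherosclerotic findings.

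**Conclusion.** The point holds as a mismatch between aims and design. Efficacy of antiplatelet therapy, efficacy of each drug, and primary prevention or occurrence of atherosclerosis are not answerable here. The effect of cilostazol relative to aspirin, in type 2 diabetic patients with findings of mild ASO, is answerable.

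The size is in interpretation: all three statements of aim need narrowing, and no figure, endpoint or test changes. The conclusion rests on the arms, the entry criteria and the article's own remark on aspirin, and needs no numerical assumption. A reader might infer that the trial is invalid or needs a third arm. That does not follow: the comparison of the two drugs is a legitimate question, and randomisation protects it.

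**What to change.** Replace the aim in the Abstract, Background and Discussion, and carry it into the analysis plan and results report:

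> To compare cilostazol with aspirin, in patients with type 2 diabetes and findings of mild ASO, on 2-year change in common carotid IMT (primary), and on internal carotid IMT, MRI-assessed cerebral infarction, cardiovascular events, death, withdrawal, ABI and safety.

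The safety and secondary objectives belong in this sentence. An aim limited to IMT would leave endpoints that the article lists without an objective.

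Add four statements:

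1. All efficacy conclusions are relative to aspirin.
2. Change over time within an arm will not be read as efficacy.
3. A non-significant difference will be reported with its confidence interval and not as equal efficacy.
4. Primary prevention of atherosclerosis is not addressed; first coronary events may be described, as a comparison between the two drugs only.

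The cost is wording and a narrower headline claim.

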### Study design and protocol

The DAPC study has been registered on the University Hospital Medical Information NetworkClinical Trials Registry (UMIN-CTR) which is a non-profit organization in Japan and meets the requirements of the International Committee of Medical Journal Editors (ICMJE). Patients enrolled in the study will have been dignosed with type 2 diabetes, aged between 40 to 85 years and with clinical findings suggestive of arteriosclerosis obliterans (ASO) (Table 1, Table 2). In the study ASO will be defined as detection of the following findings in either of the patient's lower limbs: an ABI (ankle brachial pressure index) of <1.0 and a weakened or bilaterally different pulsation of the popliteal artery or dorsal artery of the foot; or clinical signs and symptoms suggestive of ASO.

**Table 1 T1:** Enrollment Criteria

***Inclusion criteria:***
1) Type 2 diabetes mellitus
2) Age between 40 to 85 years
3) Clinical findings suggestive of arteriosclerosis obliterans (ASO)
Note 1: Definition of ASO: Patient who has the following lesions in either of the lower limbs
• ABI (ankle brachial pressure index) < 1.0
• A weakened or bilaterally different pulsation of popliteal artery or dorsal artery of foot
• clinical signs and symptoms suggestive of ASO
***Exclusion criteria:***
1) Type 1 diabetes mellitus or secondary diabetes mellitus
2) Age less than 40 or greater than 85 years
3) Severe ASO rated as Fontaine IIb or over
4) Cerebrovascular disorders rated as grade 4 or greater on the Modified Rankin Scale
5) Medical history of angina or myocardial infarction
6) Severe hepatic dysfunction (liver cirrhosis) or renal dysfunction (serum creatinine ≥ 1.5 mg/dL)
7) Congestive heart failure
8) Severe hematological abnormalities
9) Diagnosis of homologous familial hypercholesterolemia
10) Drug allergies or medical history of hypersensitivity to the investigational drugs
11) Pregnant or lactating women, or women who wish to become pregnant
12) Others whom the investigator judges inappropriate as subjects for this study

**Table 2 T2:** Study Outline

**Target number of patients: **408 patients	
**Study Design: **Randomization	Aspirin group (81–100 mg/day; Group A) Cilostazol group (100–200 mg/day; Group C)
**Follow-up: **2-year prospective follow-up study	
**Primary endpoints:**	
IMT*: Variation of right and left max IMT-CCA and mean IMT-CCA	
**Secondary endpoints:**	
IMT*: Variation of right and left max IMT-ICA	

*Variation is measured by the IMT Evaluation Committee by using a diagnostic software application called IntimaScope^® ^while the allocations are blinded.

The following exclusion criteria were set: those with type 1 or secondary diabetes, severe ASO (greater than a Fontaine IIb category) or grade 4 or higher cerebral infarction on the Modified Rankin Scale, and medical history of angina or myocardial infarction. In addition, patients with a range of concomitant comorbidities including severe hepatic or renal dysfunction, congestive heart failure, bleeding disorders, or familial hypercholesterolemia, those with allergy or hypersensitivity to the investigational drugs, pregnant or lactating women, or women wishing to become pregnant, were excluded. Written informed consent has been obtained from all patients, and the study has been reviewed by the ethics review board of the all institutes participated in this study if the institute had the ethics review board.

Registration of patients was preformed at the administration office of the Diabetic Atherosclerosis Prevention by Cilostazol (DAPC) Study via the Internet, and once enrolled, subjects were randomly assigned to the aspirin group (81–100 mg/day; group A) or the cilostazol group (100–200 mg/day; group C). Patients who were already receiving antiplatelet drugs were assigned without a washout period. The study period will be 2 years after the registration of subjects (registration period: November 2004 to March 2006; full study duration: December 2004 to March 2008).

The primary study endpoint is the change in right and left maximum IMT of the common carotid artery (CCA) and mean IMT-CCA change. Secondary endpoints are the change in right and left maximum IMT of the internal carotid artery; semiquantitative evaluation of cerebral infarction by MRI measurement; cardiovascular events including sudden death, occurrence or recurrence of stroke, transient cerebral ischemic attacks, acute myocardial infarction, angina, and progression of ASO; overall death; withdrawal; and change in ABI.

Investigations will be performed at the start of the study, after 1 year, at the conclusion of the study, and at the time of any discontinuations or changes in dosage. Any adverse reactions will also be assessed.

Statistical analysis using changes in IMT was first undertaken to determine the number of patients required to identify a significant difference between the two groups. As a result, at least 408 patients were calculated to be required to obtain a significant difference (*p *< 0.05) between the two groups. Therefore, the target number of patients was 400 for the 1-year registration period. Statistical analysis will be performed using the *t*-test to compare the change in maximum IMT, the log-rank test for incidence of events and mortality rate, and the Kaplan-Meier method to plot survival curves. Ratios of events between the 2 groups and confidence intervals are to be determined by Cox regression. A 1-way ANOVA will be used to compare ABI. The administrative office of the DAPC Study will analyze these data.

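### The statistical text sets a target of 400, below its own stated minimum of 408 and below the 408 in Table 2, with no visible allowance for loss over 2 years

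*Protocol article*

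**What the plan says.** The protocol article gives the size of the trial in three statements.

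- The statistical paragraph that closes the section on study design and protocol: "As a result, at least 408 patients were calculated to be required to obtain a significant difference".
- The next sentence of that paragraph: "Therefore, the target number of patients was 400 for the 1-year registration period".
- Table 2 (Study Outline): "Target number of patients: 408 patients".

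The calculation is said to rest on changes in IMT. The only design parameter given with it is a significance level: "to obtain a significant difference (*p *< 0.05) between the two groups". The planned comparison is a t-test: "Statistical analysis will be performed using the *t*-test to compare the change in maximum IMT". Follow-up is 2 years, and withdrawal is one of the secondary endpoints. No allowance for loss is mentioned beside either figure.

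**The concern.** A target cannot follow from a calculated minimum and also be smaller than it. The word joining the two sentences presents 400 as the consequence of 408, and Table 2 then gives 408 as the target. A reader cannot tell which number the trial set out to reach.

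The gap also bears on loss to follow-up. The primary outcome is a change in IMT, so each patient contributes only with a baseline scan and a later one. When a target is already below the calculated requirement, no room is visible for patients who lack the second scan. If 408 was the number needed in the analysis, 400 registered patients cannot supply it even with complete follow-up. If 408 was a registration figure with some allowance built in, the position is better, but the article does not say so. The power the trial can claim depends on which meaning applies.

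**Working it through.** **Inputs**

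- Calculated minimum: 408 in total (statistical paragraph).
- Targets: 400 (statistical paragraph) and 408 (Table 2).
- Significance level: 0.05 (statistical paragraph). Two-sided is assumed.
- Allocation: two randomised arms. 1:1 is assumed, so 408 is 204 per arm and 400 is 200 per arm.
- Power behind 408: not given. 80% and 90% are both shown.
- Loss: not given. 10%, 15% and 20% are shown as assumptions.

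**Step 1. Can 408 be reproduced?** Not as a test of the plan, because the article does not give the difference, SD and power behind it. The check therefore takes 408 as correct and asks what a smaller number would deliver.

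**Step 2. Standardised difference implied by 408.** For a two-sample comparison with n per arm, d = (z for 0.975 + z for power) × √(2/n). With n = 204, √(2/204) = 0.0990.

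- 80% power: (1.960 + 0.842) × 0.0990 = 0.277 (0.278 by the exact t-test).
- 90% power: (1.960 + 1.282) × 0.0990 = 0.321 (0.322 by the exact t-test).

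**Step 3. Power at 400 with no loss.** Power = Φ(d × √(n/2) − 1.960), with n = 200 and √(n/2) = 10.

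- From 80%: Φ(2.774 − 1.960) = Φ(0.814) = 79.2%.
- From 90%: Φ(3.210 − 1.960) = Φ(1.250) = 89.4%.

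The shortfall is 8/408 = 2.0% of patients and 0.6 to 0.8 points of power.

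**Step 4. Power at 400 registered, if 408 means evaluable patients.** The values are from the t-test; the normal approximation agrees to within 0.1 point.

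| Assumed loss | Evaluable (per arm) | Power if 408 gave 80% | Power if 408 gave 90% |
|---|---|---|---|
| 0% | 400 (200) | 79.2% | 89.4% |
| 10% | 360 (180) | 74.9% | 86.1% |
| 15% | 340 (170) | 72.5% | 84.1% |
| 20% | 320 (160) | 69.8% | 81.8% |

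**Step 5. The same result as a detectable difference.** At fixed power, the detectable difference grows by √(204/n).

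- n = 200: √1.020 = 1.010, or 1.0% larger.
- n = 180: √1.133 = 1.065, or 6.5% larger.
- n = 160: √1.275 = 1.129, or 12.9% larger.

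**The case against.** **The gap is trivial.** Eight patients cost less than one point of power. This stands. Without the question of loss, the point would be only a matter of consistency.

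**400 may be a first-year goal.** The sentence ties 400 to a 1-year registration period, while the same section gives registration as November 2004 to March 2006, about 17 months. On that reading 400 is an interim goal and 408 the overall target. This is possible, but it does not fit the wording, which presents 400 as what follows from the calculation. It also leaves the reader to guess, so the passages still need reconciling.

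**Loss may be smaller than feared.** The article gives no attrition rate and does not say whether 408 already includes an allowance. It also schedules investigations at 1 year and at discontinuation, so a patient who stops early may still have a later scan. This stands. A reader might infer that the evaluable number is bound to fall well below 408, but the document does not support that.

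**A condensed article may leave power and SD to the full protocol.** This stands, and their absence is not the point here.

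**A stronger reading: 408 conflicts with the quoted progression rates.** The Background reports, for aspirin, that patients "showed a slight progression of intima-media thickness (IMT) of the carotid artery (0.033 ± 0.010 mm/year", and for cilostazol that "similar patients given cilostazol showed negligible change in IMT (0.00 ± 0.16 mm/3 years". A reader might try to rebuild 408 from these, fail, and call the figure wrong or say it could mean almost any power. That does not hold, for three reasons.

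- The article offers these figures as rationale and never names them as inputs to the calculation.
- Some readings do reach 408. A 1-year difference of 0.033 mm with SD 0.16/√3 = 0.0924 and 95% power gives 2 × 12.995 × (0.0924/0.033)² = 203.7, so 204 per arm and 408 in total. This was found by searching and does not show how 408 arose, but it rules out saying that 408 cannot be obtained.
- On the 2-year scale (0.066 mm if progression is linear, SD 0.16), the totals are 186, 248 and 306 for 80%, 90% and 95% power. These are below 408, so they do not suggest 408 is too small. A low power for 408 appears only when a 1-year difference is paired with an unscaled 3-year spread.

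**Conclusion.** The contradiction is certain and visible in the text: a minimum of 408, a target of 400 said to follow from it, and a target of 408 in Table 2. The text target is below the plan's own minimum, and no allowance for loss is visible.

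Taken alone, the effect is under one point of power, given a two-sided 0.05 test and equal arms. The larger effect, roughly 4 to 10 points below the nominal power, is conditional. It requires that 408 counts evaluable patients, that nothing for loss is already inside it, and that 10% to 20% of registered patients lack a usable pair of scans. The article confirms none of these. The finding is therefore an inconsistent sample size whose meaning is left open. It does not show that the trial is underpowered or that 408 was miscalculated.

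**What to change.** 1. Give one target in both the statistical paragraph and Table 2.
2. Say whether it counts registered or evaluable patients, and whether an allowance for loss is included.
3. If 400 stays, replace the statement that at least 408 are required with the power, or the detectable difference, that 400 registered patients deliver after the expected loss.

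The cost is one calculation re-run and two places corrected. No extra enrolment is needed. The downside is that the stated power becomes slightly less favourable, or the stated detectable difference slightly larger.

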The results of this study are expected to assist in the development of appropriate drug therapies for patients with type 2 diabetes and atherosclerosis. This is a very important objective because the incidence of this common complication of diabetes is rising at a staggering rate among many Asian countries. It is expected that health systems in Asia will be severely stretched in the near future by trying to manage patients with diabetic complications, and the economic and social costs to the individuals and countries will be large. The design of this study is ground breaking in that enrollment was via the Internet and all results will be pooled by using a unique online patient registry system. Not only are all of the mathematical and demographic data to be held on this database, but also all of the images taken from the MRI assessment of cerebral changes and alterations in IMT. This is the first such online system to be developed in Asian countries for pooling data from an international clinical trial. Results will be available rapidly, and these findings are expected to provide clinical data that will help in the prevention of diabetic atherosclerosis and subsequent cardiovascular and cerebrovascular disease. Results from this important clinical trial are planned to be published in 2008.

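### The named t-test and log-rank test leave country out of a four-country pooled comparison: valid, but giving up a probably small amount of precision that is almost free to recover

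*Protocol article*

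**What the plan says.** The Background section of the Protocol article states that "a cooperative, multinational research group in Japan, Korea, China, and Phillippine has been formed", and the Discussion that "all results will be pooled by using a unique online patient registry system". The share of patients from each country is not given.

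The statistics paragraph under Study design and protocol names the tests: "Statistical analysis will be performed using the *t*-test to compare the change in maximum IMT, the log-rank test for incidence of events" and mortality. For the size of the event effect it adds: "Ratios of events between the 2 groups and confidence intervals are to be determined by Cox regression". No country or site term, and no stratum, appears with any of these.

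On assignment, the same section says that "once enrolled, subjects were randomly assigned to the aspirin group" or to the cilostazol group. It gives no ratio and no stratification factors. The primary outcome is a within-patient quantity: "The primary study endpoint is the change in right and left maximum IMT of the common carotid artery (CCA) and mean IMT-CCA change". The footnote to Table 2 says how it is read: "Variation is measured by the IMT Evaluation Committee by using a diagnostic software application called IntimaScope", with allocation blinded.

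**The concern.** Four countries may differ in how fast IMT progresses and how often events occur, for reasons unrelated to the two drugs. A two-sample t-test treats all patients as one sample, so such differences count as unexplained noise. If assignment was not balanced by country, the arms may also differ somewhat in country mix by chance, and the pooled test does not correct for it. If assignment was balanced by country, the pooled t-test ignores variation that the design has already removed, and its standard error is too large.

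What is at stake is efficiency: a wider confidence interval and somewhat lower power than the same patients could give. The t-test is a stated method that excludes a country term, so the point concerns a choice made in the document and not only detail left to a fuller plan.

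**Working it through.** **Inputs from the Protocol article:** 408 patients required; significance level 0.05; four countries; two groups; outcome analysed as change.

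**Assumptions, not in the documents:** 1:1 allocation, a two-sided test, base power of 80% (90% as an alternative), and R², the share of variance in IMT change explained by country.

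**1. The plan's own figure.** The article says that "at least 408 patients were calculated to be required to obtain a significant difference", without power, effect size, standard deviation, sidedness or dropout. The Background cites 0.033 mm/year on aspirin and 0.00 ± 0.16 mm over 3 years on cilostazol, but does not call them sample-size inputs. With n per arm = 2(z₁₋α/₂ + z₁₋β)²SD²/δ²:

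- δ = 0.033 × 2 = 0.066 mm, SD 0.16: 186 patients in total at 80% power, 248 at 90%.
- δ = 0.033 mm, SD 0.16: 740 at 80%, 990 at 90%.

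So 408 can be neither confirmed nor refuted. Taken as given, it corresponds to a standardised difference of (1.960 + 0.842) × √(2/204) = 0.277 at 80% power, or 0.321 at 90%.

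**2. Power with country in the model.** Adjustment reduces the residual SD by the factor √(1 − R²). From the 80% base, power = Φ(2.802/√(1 − R²) − 1.960). The sample size giving the same 80% power is about 408 × (1 − R²), rounded up to equal arms.

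| Assumed R² | Adjusted power, 80% base | N for 80% power | Adjusted power, 90% base |
|---|---|---|---|
| 1% | 80.4% | 404 | 90.3% |
| 2% | 80.8% | 400 | 90.6% |
| 5% | 82.0% | 388 | 91.4% |
| 10% | 84.0% | 368 | 92.7% |

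**3. Chance imbalance.** Under simple randomisation of 408, a country supplying half the patients can differ between arms by 1.96 × √(0.25 × 4/408) = 0.097, about 10 percentage points either way (95% range). To see what that does, suppose two equal halves and R² = 10%. The halves then differ by 2 × √0.10 = 0.63 SD, and a 0.097 imbalance moves the estimate by 0.097 × 0.63 = 0.06 SD. The standard error of the comparison is 2/√408 = 0.10 SD. Even an imbalance at the edge of the range is well within sampling error, and the t-test's standard error already allows for it.

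**4. Simulation.** This used 408 patients in four unequal countries (244, 82, 41, 41), R² of 2%, 5% and 10%, and 8000 runs per setting.

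- Type I error of the pooled t-test: 4.8–5.2% without stratified randomisation, 4.1–4.9% with it. There is no inflation, and the test is slightly conservative if randomisation was stratified.
- Power gain from adjustment: about 0.3–0.7 points at R² = 2%, 1.4 at 5% and 3–3.5 at 10%. This agrees with the table within simulation error.

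**5. Events.** No event rates are given, so no size can be put on the gain from stratifying the log-rank and Cox analyses.

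**The case against.** The strongest reply is that this is a preference and not an error. A t-test on change in a randomised trial is valid, and the simulation bears that out. Chance imbalance is not a separate harm, because its variability is already in the standard error. The variance share is assumed, and small values are quite possible: at 2% or less the gain is under one power point. All of this stands, and it limits the point to precision.

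It can also be said that a condensed article leaves strata and covariates to the full protocol. That stands for the Cox model, whose covariates are unstated and not excluded. It stands for the randomisation, which may have been stratified through the online system, and largely for the log-rank test, which could still be stratified. It does not stand for the t-test, which cannot carry a country term.

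A reader might go further in two directions that the documents do not support.

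- **Scanners.** One might infer that different machines and operators distort the comparison and that the same equipment should be required at every visit. The article says nothing about equipment or changes of it. A constant scanner offset cancels in a within-patient change, and one blinded committee measures IMT with one software application. Effects of a change of machine, or of variability that depends on the machine, are possible, but nothing in the article shows that they occur.
- **Little slack.** One might infer that the trial was sized too tightly to lose any precision, since the text moves from at least 408 required to a target of 400. Without the inputs to 408, the margin cannot be judged: the illustrative calculations range from well below it to well above it.

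**Conclusion.** The point holds as a matter of efficiency. The t-test and log-rank test, as named, use no country information although the data are pooled from a four-country group. They remain valid, but between-country variation in IMT progression stays in the error term.

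The loss runs from under one power point if country explains 2% or less of the variance of IMT change to about four points at 10%, from an 80% base. These figures rest on assumed variance shares, 1:1 allocation, a two-sided test and 408 analysed patients. If one country supplies nearly all patients, the gain will be near the bottom of the range. For events the size is unknown. The change is worth making because it costs so little. The validity of the trial does not depend on it.

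**What to change.** Before the comparative data are seen, replace the t-test with a linear model of IMT change on treatment with country as a fixed factor. If assignment was stratified, use the randomisation strata instead. Stratify the log-rank test and the Cox model by country where each country has enough events, and state in advance how countries with few events will be combined or handled.

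The cost is three degrees of freedom (4 − 1) out of about 406 (408 − 2) in the IMT model, and a few lines in the analysis plan. Country is presumably already recorded at online registration, so no extra patients, visits or measurements are needed. For events, the downside is a possible small loss of information where a stratum is sparse.
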